#### Data Analysis

Quantitative data will be analyzed as described under “Effectiveness Evaluation” section. Qualitative data obtained through audio recordings from the patient focus group discussions will be transcribed, then analyzed using thematic analysis aided by NVIVO software (QSR International). Data analysis will be both deductive and inductive. Deductive analysis will be guided by the CFIR and RE-AIM. Two researchers will independently conduct the initial coding after familiarization with the transcripts; thereafter, the subsequent and final coding criteria will be agreed upon by both researchers following an iterative review of emerging themes as informed by the research questions. The final sets of themes and subthemes relevant to the overall research goals will be reported and supported with verbatim quotes.

##### Addressing Missing Data

Though preventing missing data is difficult in clinical research, measures will be put in place by the researchers to minimize the occurrence of missing data. This includes having a well-defined data collection strategy that is understood by all study personnel, as well as having a simple set of questionnaires to collect only relevant data needed, minimizing the number of follow-ups with participants, and creating substantial gaps in the number of follow-ups. The investigators will identify and actively engage the participants who would be at the greatest risk of being lost during follow-up. Further, the data collection would be monitored and reported in as close to real time as possible during the study. Notwithstanding the above, the mean substitution strategy would be employed by the research team to handle missing data [48]. Here, the mean value of a variable is used in the place of the missing data value for that same variable. This allows the researchers to utilize the collected data in an incomplete data set. Questionnaires with more than 20% missing responses will be excluded.

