## Methods

### Study Design

The STEM study design is a mixed methods, hybrid type II implementation-effectiveness trial. This design evaluates the effectiveness of an implementation strategy or intervention, while also evaluating the implementation context associated with the intervention [38,39]. This study is a randomized noninferiority trial testing the outcomes for email messaging (as a strategy for delivering daily evidence-based supportive messages to patients with MDD in addition to usual care), in comparison to outcomes for text messaging, which has been deemed effective by previous studies (with noted implementation limitations [28,33]). The relevant guidelines and checklist were obtained from the Enhancing the Quality and Transparency of Health Research (EQUATOR) network website and used in the design of this trial [40]. These include the SPIRIT (Standard Protocol Items: Recommendations for Interventional Trials) checklist (Multimedia Appendix 1) and CONSORT (Consolidated Standards of Reporting Trials) guidelines (Multimedia Appendix 2) [41,42].

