### Sample Size

Based on the effect sizes (Cohen *d* of 0.85 and 0.67) achieved in 2 previous randomized trials (n<80 for each trial), which compared daily supportive text messages plus treatment as usual with treatment as usual alone for the management of patients with MDD, a sample size of 80 is estimated to have sufficient power for the current protocol. Allowing for a projected maximal 20% overall dropout rate, we propose to recruit 100 patients with MDD into the trial, with 50 patients randomly allocated into each study arm.

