### Effectiveness Evaluation

#### Hypothesis

As the same messages will be delivered through the supportive text message program and the email program, we hypothesize that daily email messaging will not be inferior to daily supportive text messaging in reducing depression symptoms and improving quality of life for patients with MDD. We further hypothesize that participant dropout rates and satisfaction rates will be comparable in the two arms of the study.

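### Mean substitution is the only stated method for missing data and its scope is left open: filling whole scores would inflate false noninferiority, filling stray items would not

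*Protocol article*

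**What the plan says.** The Addressing Missing Data section first lists measures to prevent missing data, then states that "the mean substitution strategy would be employed by the research team to handle missing data". It defines the method: "the mean value of a variable is used in the place of the missing data value for that same variable". It closes with an exclusion rule: "Questionnaires with more than 20% missing responses will be excluded". The article describes no other method for missing data and no sensitivity analysis.

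Three other sections bear on this. Study Design states "This study is a randomized noninferiority trial testing the outcomes for email messaging", and Hypothesis expects that "daily email messaging will not be inferior to daily supportive text messaging in reducing depression symptoms". Sample Size starts from 80 patients and goes to 100, 50 per arm: "Allowing for a projected maximal 20% overall dropout rate". Data Analyses, under Effectiveness Evaluation, plans a separate ANCOVA of PHQ-9 and WHO-5 at each follow-up, adjusted for baseline.

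**The concern.** The definition leaves two things open. The variable could be a single item or a total score, and the mean could be taken over all patients or within an arm.

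The choice matters because of the direction of the hypothesis. If missing total scores are filled with the overall mean, dropouts in both arms receive the same number and the arms are pulled together. In a superiority trial that costs power; in a noninferiority trial it favours the conclusion sought. If the arm mean is used, the difference is kept, but invented values count as observations and the confidence interval is too narrow. That also makes it too easy to clear a margin.

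If only stray items are filled, an unreturned questionnaire is dropped. The analysis at that week is then restricted to completers, and the patient's earlier follow-up scores contribute nothing to it.

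**Working it through.** **The plan's own figure.** 80 / (1 − 0.20) = 100, which matches the recruitment target.

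**Inputs from the article.** n = 50 per arm; missing share p = 0.20 (the stated maximum); baseline-adjusted ANCOVA at each week.

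**Inputs assumed, because the article states none.** One-sided level 0.025 (upper limit of a 95% interval); margin M from 0.30 to 0.67 SD (0.67 is the smaller cited effect, and 0.335 is half of it); baseline correlation 0.5; data missing completely at random in equal shares. The true difference is set at M, so every declaration of noninferiority is false.

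**Whole scores filled, closed form without covariate (SD = 1).**

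*Arm mean.* True SD of the estimate = √(2/40) = 0.2236. Reported SE = √(0.8 × 2/50) = 0.1789, and 0.1789/0.2236 = 0.80, so it is 20% too small. False-noninferiority rate = Φ(−1.96 × 0.80) = Φ(−1.568) = 0.058 at any margin.

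*Overall mean.* The filled values cancel between arms, so the expected estimate is 0.8M, with SD 0.8 × 0.2236 = 0.1789. Reported SE = √{(2/50)[0.8 + 0.8 × 0.2 × M²/4]}. Rate = Φ((0.2M − 1.96 × SE)/0.1789).
- M = 0.30: SE 0.1793; Φ(−1.63) = 0.052
- M = 0.335: SE 0.1794; Φ(−1.59) = 0.056
- M = 0.50: SE 0.1800; Φ(−1.41) = 0.079
- M = 0.67: SE 0.1809; Φ(−1.23) = 0.109

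**Whole scores filled, simulated ANCOVA (10,000 trials per setting, p = 0.20).**

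| Margin (SD) | Observed data only | Overall mean | Arm mean |
|---|---|---|---|
| 0.335 | 0.023 | 0.060 | 0.058 |
| 0.50 | 0.025 | 0.090 | 0.060 |
| 0.67 | 0.025 | 0.126 | 0.060 |

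At a true difference of 0.50, overall-mean filling estimates 0.40. Arm-mean filling reports an SE of 0.160 against a true SD of about 0.20. Observed-data ANCOVA reports 0.194 against a true SD of 0.193 to 0.196. At 10% missing, the rates are 0.042 to 0.056 (overall mean) and 0.037 to 0.040 (arm mean).

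**Only stray items filled.** The exclusion rule allows at most 1 of 9 PHQ-9 items (1/9 = 11%; 2/9 = 22% is over) or 1 of 5 WHO-5 items (exactly 20%). With 20% dropout excluded, M = 0.50 and 2% to 5% of items missing, overall item-mean filling gives 0.026 to 0.030. With no items missing the rate is 0.025.

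**Completers only, dropout dependent on 6-week symptoms.** Two sets of simulations at about 20% dropout assumed different correlations (0.5 to 0.6 in one; 0.7 between weeks 6 and 24 in the other).
- Same dependence in both arms: 0.024 to 0.036.
- Dependence stronger in, or confined to, the email arm: 0.043 to 0.057. In the upper case a true 0.50 was estimated as 0.43. As a rough check with the SE of 0.194 from above, Φ(0.07/0.194 − 1.96) = Φ(−1.60) = 0.055. A likelihood-type estimate that used the 6-week score recovered 0.50.

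**The case against.** The strongest objection is that the text favours the item-level reading. An unreturned questionnaire is 100% missing and falls under the exclusion rule, and raising 80 to 100 for dropout makes most sense if about 80 observed patients are analysed. On that reading mean filling does almost no harm. This stands, and it rules out a stronger inference that a reader might draw: that the plan carries a proven inflation of two- to five-fold, or that it is unsound on every reading. The documents support neither. Completers-only ANCOVA holds its level when data are missing completely at random, and nearly so when dropout works alike in both arms.

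The item-level reading is nevertheless not stated. The definition speaks only of a variable, and the section gives the purpose as making use of an incomplete data set.

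Other points stand in part:
- 20% is a maximum, and the article plans reminders after 3 days and completion by telephone. At 10% missing the whole-score rates fall to about 4% to 6%.
- The section sits under Implementation Evaluation, so its application to the primary ANCOVA is likely but not explicit.
- Whether the mean is overall or by arm could be settled in an analysis plan not shown here. Mean substitution itself, however, is stated in this article and is not left to such a plan.
- Using earlier scores is partly a matter of efficiency. It becomes a matter of bias only if dropout depends on those scores.

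**Conclusion.** The point holds conditionally. The only stated method for missing data leaves its scope open, and the readings differ several-fold in error rate.

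- **Whole scores filled at 20% missing:** false noninferiority of about 5% to 13% with the overall mean, rising with the margin, and about 6% with the arm mean, against 2.5%.
- **Stray items filled:** about 2.6% to 3.0%. The remaining risk then comes from dropping unreturned questionnaires. The rate stays close to nominal unless dropout depends on earlier symptoms differently by arm, where the simulations gave about 4% to 6%. Such a difference is plausible, because survey links go out through the assigned channel (Randomization and Blinding).

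The margin, level, correlations and dropout mechanisms are all assumptions, so no single rate belongs to this trial. What does not depend on the margin is the direction: where filling or arm-dependent dropout mattered in these settings, it favoured the trial's own hypothesis.

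**What to change.** Before follow-up scores are analysed:

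1. Remove mean substitution for missing assessments.
2. Analyse PHQ-9 and WHO-5 with a likelihood-based repeated-measures model (arm, week, arm-by-week, baseline-by-week) on all observed follow-up scores, reading the arm contrast at each week. Alternatively, keep the planned ANCOVA and precede it with multiple imputation by arm that includes baseline and earlier scores. Multiple imputation was not simulated here.
3. For questionnaires with at most 20% missing items, prorate from that patient's own answered items.
4. Add one sensitivity analysis that worsens missing email-arm scores in steps, to show how far the noninferiority conclusion survives.
5. State that these rules apply to the effectiveness outcomes as well as the implementation data.

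The cost is revised wording and slightly more analysis work, with no new data, patients or visits.

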##### Gender Analysis

Gender analyses will guide the entire study. Beyond gender disaggregation and adjustments to accommodate potential differences in subscription, the development and adaptation of the supportive messages will receive input from gender specialists. Further, the implementation science framework CFIR is designed to accommodate and understand gender among the characteristics of individuals involved in intervention implementation.

### Ethics and Dissemination

All study participants will be provided with an information leaflet and offered the opportunity to ask questions about the study before being asked to provide written informed consent to participate in the study. Data collection will occur online through patient self-completed rating scales. The study has received institutional review board approval from the University of Alberta Human Ethics Review Board (Pro00105429), and the trial has been registered at ClinicalTrials.gov (NCT04638231). Results will be disseminated as publications, conference presentations, and stakeholder policy dialogues.

## Results

Data collection for this trial began in April 2021. We expect the study results to be available within 18 months of study commencement. The findings of the trial are expected to shed light on the feasibility, acceptability, and effectiveness of using automated emails as a strategy for delivering supportive messages to patients with MDD in comparison to text messaging.

## Discussion

### Implications of the Study

Supportive messaging may be effective for providing patient support for various mood disorders. It is accepted that this intervention can reduce demand for physical mental health services, particularly the need to seek acute mental health care at emergency departments [28,30,33].

As previous studies have delivered these messages using text messaging services on mobile devices, this study seeks to examine the effectiveness of email-based delivery of equivalent messages. The STEM trial will provide comparative evidence on both delivery strategies as well as useful information to inform us on how to better implement them at scale. Findings from this study will be useful for mental health professionals managing MDD, and will contribute to knowledge on eHealth approaches generally. During the current COVID-19 pandemic, this is particularly important as health care agencies seek alternatives to physical contact where possible [49,50].

The external validity of this trial is limited by the single catchment site context. Despite this, findings from this trial will inform the implementation of a planned full-scale multicenter clinical trial using Resilience N Hope [51] to determine the effectiveness of this strategy across various contexts. The limitations are mitigated by the mixed methods approach to the design. It is hoped that the triangulation of findings from both quantitative and qualitative methods will provide useful insights. In addition, the proposed application of implementation science frameworks will provide practical information to inform implementation at scale. Unavoidably, the study sample might experience a considerable selection bias, based upon the necessity of having a functioning mobile phone and an email address in order to be able to participate in the study. Thus, this bias may limit the generalizability of our findings as patients who lack these prerequisites will not necessarily be represented in here.

### Conclusion

The STEM trial is expected to inform effective and contextually feasible strategies for delivering supportive messages to patients with MDD. The outcome of this trial will have translational impact on routine patient care and access to mental health as well as potentially support mental health policy decision-making for health care resource allocation.

## Appendix

Multimedia Appendix 1 The SPIRIT checklist.

Multimedia Appendix 2 CONSORT 2010 checklist.

## Abbreviations

ANCOVA: analysis of covariance
BDI-II: Becks Depression Inventory-II
CFIR: Consolidated Framework for Implementation Research
CONSORT: Consolidated Standards of Reporting Trials
DSM-5: Diagnostic and Statistical Manual of Mental Disorders
EQUATOR: Enhancing the Quality and Transparency of Health Research
GAD-7: Generalized Anxiety Disorder-7
MDD: major depressive disorder
PHQ-9: Patient Health Questionnaire-9
RE-AIM: Reach, Effectiveness, Adoption, Implementation, and Maintenance
SPIRIT: Standard Protocol Items: Recommendations for Interventional Trials
STEM: Supportive Text vs Email Messaging
WHO-5: 5-item World Health Organization Well-Being Index
